## Abstract

**Background::**

Heart failure (HF) is the final stage of various cardiac diseases with poor prognosis. The integrated traditional Chinese medicine (TCM) and western medicine therapy has been considered as a prospective therapeutic strategy for chronic heart failure (CHF). There have been small clinical trials and experimental studies to demonstrate the efficacy of Shenfu Qiangxin Pills (SFQX) for treating CHF, however, there is still a lack of further high-quality trial. This paper describes the protocol for the clinical assessment of SFQX in CHF (heart-kidney Yang deficiency syndrome) patients.

**Methods::**

A randomized, double-blind, parallel-group, placebo-controlled, multi-center trial will assess the efficacy and safety of SFQX in the treatment of CHF. 352 patients with CHF (heart-kidney Yang deficiency syndrome) from 22 hospitals in China will be enrolled. Besides their standardized western medicine, patients will be randomized to receive treatment of either SFQX or placebo for 12 weeks. The primary outcome is the plasma N-terminal pro-B-type natriuretic peptide levels, which will be measured uniformly by the central laboratory. The secondary outcomes include composite endpoint events (hospitalization due to worsening HF, all-cause mortality, other serious cardiovascular events), echocardiography indicators, grades of the New York Heart Association (NYHA) functional classification, the 6-minute walk test (6MWT) results, Minnesota Living With Heart Failure Questionnaire and TCM syndrome scores.

**Discussion::**

The integrated TCM and western medicine therapy has developed into a treatment model in China. The rigorous design of the trial will assure an objective and scientific assessment of the efficacy and safety of SFQX in the treatment of CHF.

**Trial registration::**

Chinese Clinical Trial Registry: ChiCTR2000028777 (registered on January 3, 2020).

## Introduction

1

Heart failure (HF), as the final stage of various cardiac diseases, is an abnormality of cardiac structure or function.^[1]^ Evidence from China Heart Failure (China-HF) Registry has demonstrated that in-hospital mortality is 4.1% ± 0.3%.^[2]^ Over the last 3 decades, amelioration of treatments and implementation have improved survival and reduced the hospitalization rate in patients with heart failure with reduced ejection fraction (HFrEF).^[3]^ According to the guidelines for chronic heart failure (CHF) treatment, angiotensin receptor neprilysin inhibitor, angiotensin-converting enzyme inhibitors or angiotensin receptor blockers, beta-blockers, aldosterone receptor antagonists, diuretics, digitalis, and vasodilating agents are standard treatments for heart failure.^[4]^ However, the outcomes often remain unsatisfactory. Traditional Chinese medicine (TCM) has the characteristics of multi-target, multi-function and multi-pathway in the process of prevention and treatment of HF. The integrative treatment of western medicine and TCM for HF is associated with increased quality of life, low re-admission rate, and favorable prognosis.^[5]^

China guidelines for the diagnosis and management of heart failure published in 2014 and 2018 all cited evidence from clinical studies of TCM, so more attention has been paid to TCM and it has been widely used in clinical practice. Shenfu qiangxin pills (SFQX, produced by Tianjin Zhongxin Pharmaceutical Group Corporation LTD. Darentang Pharmaceutical Factory), a patent drug made of Ginseng(Renshen), Radix aconiti carmichaeli (Fuzi), rhubarb (Dahuang), the root bark of white mulberry (Sangbaipi), Polyporus umbellata, Semen lepidii (Tinglizi), grifola (Zhuling), have the effects of nourishing Qi, warming Yang, strengthening heart, and promoting diuresis. The pills have been commonly used in TCM for the integrative treatment of patients with CHF who are also diagnosed with heart-kidney Yang deficiency syndrome characterized with palpitations, breathlessness, chest tightness, puffy face and swollen limbs. Experimental researches have shown in animal models that SFQX could reduce water-sodium retention, correct electrolyte disturbance, protect renal and cardiac function via attenuating autophagy and apoptosis.^[6–8]^ Some small-scale clinical studies indicated that SFQX had the advantages of enhancing cardiac contractility and improving heart function.^[9,10]^

However, the explicit role of SFQX in preventing and treating cardiovascular disease remains unclear due to a lack of sound scientific evidence. Currently available randomized controlled trials on SFQX are flawed, with small sample sizes, making it difficult to draw definite conclusions on the actual benefits and harms of it.^[11]^ Hence, further rigorously designed randomized controlled trials are warranted to assess the effect of SFQX in patients with CHF so as to provide high-quality evidence for clinical practice.

We would like to test the hypothesis that patients with CHF will benefit from SFQX and evaluate its safety through a high-quality clinical trial.

## Methods

2

### Objectives

2.1

The main objective of this study is to evaluate the safety and efficacy of SFQX so as to provide high-quality research evidence for its clinical practice compared to placebo for treating CHF.

### Study design and setting

2.2

This study is designed as a randomized, double-blind, parallel-group, placebo-controlled, multi-center trial. There are 22 institution hospitals located in different areas of China in this trial. A total of 352 stable patients with CHF, who fulfill the inclusion and exclusion criteria, will be randomized into either an experimental or control group in the ratio of 1:1. The general design of this study is demonstrated in Figure 1.

**Figure 1 F1:**
[figure not shown]
Flowchart of the study. 6MWT = 6-minute walk test, CHF = chronic heart failure, ECG = electrocardiogram, LVEF = left ventricular ejection fraction, MLHFQ = Minnesota Living With Heart Failure questionnaire, NT-proBNP = N-terminal pro-B-type natriuretic peptide, NYHA = New York Heart Association, SFQX = Shenfu Qiangxin pills, TCM = traditional Chinese medicine.

### Participants

2.3

#### Recruitment

2.3.1

Recruitment of the participants began in January 2020 and is expected to be finished in December 2021. Recruitment may be extended depending on registration completion. All participants will be given an informed consent form with a detailed explanation before enrollment, and notified that they may be withdrawn from the trial at any point without penalty. Participants can be recruited directly or openly during the clinical practice or through screening the database.

#### Diagnostic criteria

2.3.2

(1)Western medicine diagnostic criteria: refer to the 2018 guidelines for the diagnosis and treatment of heart failure in China.^[1]^(2)TCM syndrome diagnostic criteria : refer to the 2014 expert consensus on diagnosis and treatment of TCM in CHF and 2016 expert consensus on diagnosis and treatment of integrated traditional and western medicine in CHF.^[5,12]^

#### Inclusion criteria

2.3.3

(1)Participants who meet the diagnostic criteria of CHF, and have a history of CHF for more than 3 months or clinical symptoms of HF for more than 3 months.(2)Participants with heart-kidney Yang deficiency syndrome based on differentiation of syndromes and treatment.(3)Aged 18 to 80 years.(4)Left ventricular ejection fraction (LVEF) < 40%.(5)New York Heart Association (NYHA) class II to IV.(6)N-terminal pro-B-type natriuretic peptide (NT-proBNP) ≥450 pg/ml.(7)Participants who have received standardized western medicine treatment with the optimal therapeutic dose for at least 2 weeks.(8)Participants who have not used TCM for heart failure within 2 weeks before enrollment.(9)Submitted informed consent.

##### Exclusion criteria

2.3.3.1

(1)Participants who have undergone coronary revascularization and cardiac resynchronization therapy within 12 weeks or cardiac resynchronization therapy planned within 12 weeks.(2)Participants with severe primary diseases such as liver and kidney hematopoiesis and so on; alanine transaminase, aspartate transaminase, alkaline phosphatase, and/or serum creatinine values that are 2 times higher than the normal upper limit; serum potassium content >5.5 mmol/L; patients with tumor, severe neuroendocrine diseases and mental illnesses, etc.(3)Participants with left ventricular outflow tract obstruction, acute myocarditis, hypertrophic cardiomyopathy, restricted cardiomyopathy, aortic aneurysm, arterial dissection, congenital heart disease, severe arrhythmia, and significant hemodynamic changes in unrepaired heart valve disease(4)Participants with uncontrolled hypertension, systolic blood pressure ≥180 mmHg and/or diastolic blood pressure ≥100 mmHg.(5)Participants with severe peripheral arterial disease, acute attack of chronic obstructive pulmonary disease, pulmonary vascular disease such as primary pulmonary hypertension or pulmonary hypertension due to autoimmune disease.(6)Participants who are pregnant or preparing for pregnancy and lactation.(7)Participants with an allergic constitution, known sensitivity to the study drugs or their ingredients.(8)Participants in other clinical trials within 1 months.

### Study procedure

2.4

The participants who provide written informed consent and meet the inclusion and exclusion criteria will be selected at the screening visit, namely visit 1. Eligible participants will be informed via telephone call and will be asked to visit the trial center within 1 week (visit 1). At visit 1, the investigator will record demographic information, other medical history and medication, vital signs, physical examination and so on, and subjects will be randomized to the experimental or control group. The dosage used in this study is 5.4 g (2 bags) of SFQX or placebo 3 times daily for 12 weeks. Tests and assessments will be performed according to the following schedule: Visit 2 (NT-proBNP, echocardiography, NYHA functional classification, 6MWT, Minnesota Living With Heart Failure questionnaire (MLHFQ), TCM syndrome scores, composite endpoint events, complete blood count, routine urine test, liver function test, renal function test, serum electrolytes, 12-lead electrocardiogram); Visit 3 and Visit4 are the same as above. Detailed assessment schedules are outlined in Figure 2.

**Figure 2 F2:**
[figure not shown]
Study visits. A. All tests related to subjects should be carried out after signing the informed consent. B. Patients’ current chronic and acute diseases (referred to as concomitant diseases) will be recorded, along with any history information (referred to as medical history) that the researchers consider meaningful for chronic heart failure and this study. C. At the time of enrollment, the test result of NT-proBNP is based on the laboratory test standard of the sub-central research institutions. Meanwhile, spare samples will be collected and sent to the central laboratory in Beijing for measurement; the statistical results during the visit period are based on the test standard of the central laboratory. D. Composite endpoint events will be recorded at any time, including hospitalization due to worsening heart failure, all-cause mortality, and other serious cardiovascular events. E. Complete blood count includes white blood cell count, red blood cell count, hemoglobin, platelet. F. Routine urine test includes urine leukocytes, urine protein, urine latent blood, urine glucose. G. Liver function test includes alanine aminotransferase, aspartate transaminase, total bilirubin, r-glutamyl transferase, alkaline phosphatase. H. Renal function test includes serum creatinine, blood urea nitrogen. I. Electrolytes include serum potassium, serum natrium, serum chlorine. J. During the screening period, women of childbearing age can be included in the group only when the pregnancy test result is negative; during the study period, contraceptive measures are adopted voluntarily. K. The test results within 7 days before enrollment can be used as baseline data.

### Intervention

2.5

The shape and appearance of SFQX and placebo are the same: tan herbal pills. Each bag of pills is manufactured at a dosage of 2.7 g, with shelf-life of 18 months. The manufacturing company (Tianjin Zhongxin Pharmaceutical Group Corporation LTD. Darentang Pharmaceutical Factory) follows the regulations for good clinical practice, and controls the quality of the products using their own standards and testing methods.

The principle investigator will receive the products used for this trial from the company and supply them to the drug administrator. The drugs for each subject are in a box consisting of three packages (1 package for each visit period) which are labelled. A package, which includes 168 bags for 28 days plus 18 bags for spare will be prepared at 4-week intervals from visit 1 to 3. All products used in the trial will be recorded, including the amount of the medication, the date of the delivery, and the date of return.

After randomization, the participants will begin taking 5.4 g (2 bags) of SFQX or placebo orally combined with standardized western medicine treatment 3 times daily after meals for 12 weeks.

### Randomization, blinding

2.6

The central random method is used in this trial where IWRS system is used for central randomization and the assignment scheme is hidden. A block dynamic randomization method is used for randomized allocation. Randomized code generation and drug blinding will be implemented independent of the data. The trial is double-blind where the placebo is the same as SFQX in shape, color, smell, properties, and so on. Both the participants and the investigators will be blinded until completion of the trial.

### Sample size calculation

2.7

The sample size calculation is based on the proportion of patients with a decrease of NT-proBNP level by at least 30%. According to the reference, 47.95% of the patients in the qili qiangxin capsule group had reductions in NT-proBNP levels by at least 30%, compared with 31.98% of patients in the placebo group.^[13]^ We assume the proportion of patients demonstrating a decrease in NT-proBNP level by at least 30% in the treatment group would be 48%. Therefore, given a type I error rate of α = 0.05, a power of 80% (type II error rate of β = 0.20), the sample size of each group is 146 cases calculated by PASS11 software. Moreover, considering a dropout rate of approximately 20% for randomized patients, a total of 352 patients (experimental group = 176, control group = 176) is required to be randomized for the efficacy analysis.

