### Statistical analysis

2.8

The statistical significance of this study is conducted by 2-sided test and *P* < .05 is considered statistically significant. Statistics software SAS 9.4 will be used for the data analysis. Measurement data are analyzed by paired *t* test, variance analysis, rank sum test, and so on. Enumeration data are analyzed by chi-square test, Fisher exact test, etc. Ranked data are analyzed by Ridit or Cochran-Mantel-Haensel. The analysis data set will be selected from full analysis set, per-protocol set and safety analysis set. Considering the influence of baseline value, covariance analysis or logistic regression analysis will be used to deduct the baseline factor.

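### Section 2.7 allows for 20% dropout by multiplying 146 by 1.20 instead of dividing by 0.80, so 352 patients cover about 17% dropout at 80% power, not 20% (minor)

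*Protocol article*

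**What the plan says.** The trial is sized on the proportion of patients whose NT-proBNP falls by at least 30%. Section 2.7 (Sample size calculation) takes 48% for the SFQX arm. For control, the only rate it gives is the one from the cited trial of another product: "compared with 31.98% of patients in the placebo group". The error rates are set by "given a type I error rate of α = 0.05, a power of 80% (type II error rate of β = 0.20", and section 2.8 (Statistical analysis) makes testing two-sided: "The statistical significance of this study is conducted by 2-sided test". Section 2.2 fixes 1:1 allocation.

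The result before dropout is: "the sample size of each group is 146 cases calculated by PASS11 software". The allowance for dropout follows at once: "considering a dropout rate of approximately 20% for randomized patients, a total of 352 patients (experimental group = 176, control group = 176". The total of 352 is repeated in the abstract and in section 2.2. No other reason for 176 per arm is given.

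**The concern.** A dropout rate can be expressed against the number randomized or against the number who must remain. The two need different arithmetic. Section 2.7 names the first: the rate applies to randomized patients. To keep *n* evaluable after losing a fraction *d* of those randomized, *n* is divided by 1 − *d*. The stated 176 fits multiplication by 1 + *d* instead, and that always gives too small a number.

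What is at stake is whether the sample size statement is true under its own assumptions. The 146 is the minimum for 80% power and has no reserve, so any loss beyond what 176 can absorb takes power on the sizing measure below the stated target.

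**Working it through.** **Inputs.** p1 = 0.48 and p2 = 0.3198 (section 2.7; 0.32 if rounded); α = 0.05 and power 80% (section 2.7); two-sided test (section 2.8); 1:1 allocation (section 2.2); dropout d = 0.20 of randomized patients (section 2.7). The control rate is not restated as this trial's own assumption, but it is the rate that reproduces the plan's figure.

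**Step 1: reproduce 146.** With the pooled-variance z-test for two proportions and p̄ = (p1 + p2)/2:

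n = [1.96·√(2p̄(1 − p̄)) + 0.8416·√(p1(1 − p1) + p2(1 − p2))]² / (p1 − p2)²

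- 48% vs 32%: [1.96·√(2 × 0.40 × 0.60) + 0.8416·√(0.48 × 0.52 + 0.32 × 0.68)]² / 0.16² = 145.98, so 146.
- 48% vs 31.98%: 145.60, so 146.

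The stated 146 is confirmed.

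**Step 2: find where 176 comes from.**

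- Multiplying: 146 × 1.20 = 175.2, rounded up to 176. This matches the plan.
- Dividing: 146 / (1 − 0.20) = 182.5, rounded up to 183 per arm, or 366 in total.
- Difference: 7 per arm and 14 in total; 14/352 is about 4%.

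Seen another way, the 30 patients added per arm are 30/146 = 20.5% of the evaluable number but only 30/176 = 17.0% of those randomized.

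**Step 3: what 176 per arm leaves.**

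- After a 20% loss: 176 × 0.80 = 140.8, about 141 per arm.
- Largest dropout that still leaves 146: 1 − 146/176 = 17.0%.

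**Step 4: power.** With the same test,

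Power = Φ{[√n·(p1 − p2) − 1.96·√(2p̄(1 − p̄))] / √(p1(1 − p1) + p2(1 − p2))}

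| Evaluable per arm | 48% vs 32% | 48% vs 31.98% |
|---|---|---|
| 146 | 80.0% | 80.1% |
| 141 (20% of 176 lost) | 78.6% | 78.7% |

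The loss is 80.0 − 78.6 = 1.4 points (80.1 − 78.7 = 1.4 with the unrounded control rate).

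**The case against.** The strongest reply is that this hardly matters. The loss of 1.4 points is smaller than the uncertainty in the inputs, since both response rates come from a trial of a different product. With 140.8 per arm, a control rate of 31.5% would give 81.1% power and one of 32.5% would give 75.8%. This stands, and it is why the point is rated minor.

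A second reply is that the 20% is only approximate, and that the stated figures agree for any dropout up to 17.0%. That softens the point but does not remove it. The exact match to 146 × 1.20 shows that the 176 came from the wrong operation, not from a lower assumed dropout.

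A third reply is that dropouts need not be lost to the analysis. Section 2.8 names a full analysis set beside the per-protocol set, and section 2.4 schedules NT-proBNP at several visits. If all 176 per arm contributed at the assumed rates, power would be about 86.8%. The article does not fix this handling, which is commonly left to the full protocol or SAP. The reply is therefore fair as a limit on the conclusion, although section 2.7 itself treats dropouts as lost when it enlarges 146 to allow for them.

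Two stronger readings are tempting. A reader might infer that the design is simply underpowered. The documents support that only on two conditions: dropout above 17.0%, and every dropout missing from the analysis. A reader might also suppose that dropouts will be kept and counted as non-responders, and so arrive at a much lower power. The article states no such rule. Nor does it say whether the 48% and 31.98% are rates among completers; if they already count missing values as failures, discounting them again would be double counting. That question is also separate from the inflation step, because it would lower power at 183 per arm too.

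**Conclusion.** The point holds as a minor error in a stated figure. Under section 2.7's own description of dropout, 146 evaluable per group calls for 183 randomized per arm (366 in total), not 176 (352). At 20% dropout, 352 patients leave about 141 per arm and about 78.6% power (78.7% with the quoted control rate), against the stated 80%. At 80% power they cover dropout of at most 17.0%.

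This rests on three assumptions: the response rates in section 2.7 apply to those analysed, dropout is equal in both arms, and dropouts do not enter the analysis. It concerns only the responder proportion, the measure on which the trial was sized. The primary test is not affected, and recruitment need not change.

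**What to change.** Keep 352 and correct the sentence in section 2.7, for example: *352 randomized patients (176 per arm) allow for about 17% dropout at 80% power; at 20% dropout (about 141 evaluable per arm) power is about 78.6%.* The abstract and section 2.2 can stay as they are.

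The cost is one sentence and a slightly less favourable stated figure. If the sponsor prefers to keep both 20% dropout and 80% power, the consistent total is 366, which costs 14 more patients. For a gap of this size the wording change is enough.

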### Statistical analysis

2.8

The statistical significance of this study is conducted by 2-sided test and *P* < .05 is considered statistically significant. Statistics software SAS 9.4 will be used for the data analysis. Measurement data are analyzed by paired *t* test, variance analysis, rank sum test, and so on. Enumeration data are analyzed by chi-square test, Fisher exact test, etc. Ranked data are analyzed by Ridit or Cochran-Mantel-Haensel. The analysis data set will be selected from full analysis set, per-protocol set and safety analysis set. Considering the influence of baseline value, covariance analysis or logistic regression analysis will be used to deduct the baseline factor.

### Efficacy assessment

2.9

#### Primary outcome

2.9.1

The primary outcome is NT-proBNP, Efficacy assessment of primary outcome is based on either the change in NT-proBNP level or the proportion of the patients with NT-proBNP level decreased by at least 30% from baseline to 12 weeks.

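### The primary outcome is either the change in NT-proBNP or the ≥30% responder proportion, each testable at 5%, so the type I error is not held at 5%

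*Protocol article*

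**What the plan says.** Section 2.9.1 names NT-proBNP as the primary outcome and then says that its assessment is "based on either the change in NT-proBNP level or the proportion of the patients with NT-proBNP level decreased by at least 30" per cent, from baseline to 12 weeks.

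Three other places bear on the choice:

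- **Abstract, Methods:** "The primary outcome is the plasma N-terminal pro-B-type natriuretic peptide levels". This names the biomarker but not the measure of effect.
- **Section 2.7:** "The sample size calculation is based on the proportion of patients with a decrease of NT-proBNP level by at least 30" per cent. The inputs are 48% on treatment, against a control rate taken from a reference trial ("compared with 31.98% of patients in the placebo group"), "given a type I error rate of α = 0.05, a power of 80% (type II error rate of β = 0.20"). The result is 146 per group, raised to 176 per group (352 in all) for dropout.
- **Section 2.8:** testing is "conducted by 2-sided test and *P* < .05 is considered statistically significant". This is a general criterion. The section contains no order of tests, alpha split, both-must-succeed rule or other multiplicity adjustment.

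**The concern.** The between-arm difference in a continuous change and the difference in the proportion passing a 30% cut-off are separate endpoints. They can give different verdicts on the same patients. With an either/or definition and a single 5% criterion, the trial has two routes to a positive result. Testing both and claiming success on either has the same error rate as looking at both and then declaring the better one primary.

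This affects the trial's main efficacy claim. The 5% error rate that a reader would attach to that claim does not apply. Nor does the 80% power apply to whichever endpoint is used, because the article gives no effect size or standard deviation for the change in NT-proBNP.

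**Working it through.** **1. Reproduce the plan's figure.** Inputs from section 2.7: p1 = 0.48, p2 = 0.32 (31.98% rounded), two-sided α = 0.05, power 80%. Pooled-variance formula without continuity correction:

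n = [z(0.975)·√(2·p̄·q̄) + z(0.80)·√(p1q1 + p2q2)]² / (p1 − p2)², with p̄ = 0.40

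- z(0.975)·√(2 × 0.40 × 0.60) = 1.960 × 0.6928 = 1.358
- z(0.80)·√(0.2496 + 0.2176) = 0.8416 × 0.6835 = 0.575
- n = (1.358 + 0.575)² / 0.0256 ≈ 146 per group

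This matches the stated 146 exactly. The responder test uses the whole 0.05, and no alpha is reserved for a second test.

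**2. Limits on the error with two tests at 0.05.** The Bonferroni ceiling is 0.05 + 0.05 = 0.10. Under independence it is 1 − 0.95² = 0.0975.

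**3. Correlated tests.** The chance under no effect that at least one of two standard normal statistics exceeds 1.96 in absolute value:

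| Correlation (absolute) | At least one P < .05 |
|---|---|
| 0.5 | 9.1% |
| 0.7 | 8.3% |
| 0.8 | 7.8% |
| 0.9 | 7.0% |

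A plausible correlation can be worked out for the log scale. If the log change is normal and 32% of patients respond, its correlation with the responder indicator is φ(z)/√(p(1 − p)), with z = −0.468. That is 0.3576 / √(0.32 × 0.68) = 0.3576 / 0.4665 = 0.77, whatever the standard deviation.

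**4. Simulation under no effect.** NT-proBNP is taken as log-normal with 32% responders in both arms. The standard deviations are assumptions. The first set uses 141 per arm, which is 176 × 0.8 = 140.8, the number left after the planned 20% dropout. The second uses the stated 146.

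| Tests allowed | Per arm | Assumed SDs (log scale) | At least one P < .05 |
|---|---|---|---|
| Responder chi-square alone | 141 | baseline 0.8–1.0, change 0.6–0.8 | 4.7–5.3% |
| Log-scale ANCOVA alone | 141 | as above | 4.4–4.9% |
| Responder or log-scale ANCOVA | 141 | as above | 7.4–8.5% |
| Responder or raw-scale ANCOVA | 141 | as above | 8.3–9.3% |
| Responder or t test on log change | 146 | change 0.7 | 8.3% (correlation 0.77) |
| Responder or t test on raw change | 146 | baseline 0.6–1.1, change 0.5–0.9 | 8.5–9.2% (correlation about 0.3–0.5) |

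The responder and log-scale ANCOVA tests each stay close to 5% on their own; the excess comes from allowing either. The first set has 4,000 replicates per scenario, so the simulation standard error near 8% is √(0.08 × 0.92 / 4000) ≈ 0.4 percentage points.

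**5. What each remedy does to the responder test.**

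- Responder proportion as the single primary: α stays 0.05, and 146 per group gives 80.0% power.
- Both endpoints kept as alternatives at 0.025 each: z rises to 2.241, so n = (2.241 × 0.6928 + 0.575)² / 0.0256 ≈ 177 evaluable per group. At 146 per group the power is Φ[(0.16 × √146 − 1.553) / 0.6835] = Φ(0.557) = 71.1%.

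**The case against.** The strongest reply is that section 2.7 already shows the intent. The trial is sized on the responder proportion alone, at full alpha, and an analysis plan that is not shown could confirm it as decisive or set an order of testing. That softens the point but does not remove it. Section 2.7 does not say that this version decides the trial, and section 2.9.1, which defines the primary outcome, admits the other version as an alternative. Models and transformations are commonly left to an analysis plan. The identity of the primary endpoint is a protocol matter, and here it is stated, as a choice of two.

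Four narrower objections stand and limit the claim:

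- The error is not unbounded. Two tests at 5% cannot exceed 10%, and the correlation brings it lower. The accurate statement is that it is not held at the stated 5%.
- If log ANCOVA, raw ANCOVA and an unadjusted raw comparison are all left open beside the responder test, simulation gives 10.5–12.4%. That arises from the open list of methods in section 2.8, not from the either/or wording, and the conclusion does not use it.
- The abstract does not contradict section 2.9.1. It names the biomarker, and fails to settle the measure.
- Other rules would also restore 5%: both must succeed, a fixed order, or an alpha split.

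**Conclusion.** The concern holds. As written, the protocol allows the primary claim to rest on either of two endpoints at an undivided two-sided 0.05. The resulting type I error is about 7% to 9% against a stated 5%, with a ceiling of 10%. The 7–9% range depends on assumed correlations and standard deviations, since the documents give none; every scenario examined exceeded 5%. That the error is not held at 5% follows from the wording and does not depend on those assumptions. The planned 80% power applies to the responder proportion only. This must be corrected before unblinding, because a choice of endpoint made once results are known would not be credible.

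**What to change.** In section 2.9.1, replace the either/or wording with one primary endpoint: the proportion of patients with a fall of at least 30% in central-laboratory NT-proBNP from baseline to week 12. This is the natural choice because the 352 patients were sized on it. State the same endpoint in the abstract's definition. Specify the central-laboratory value at baseline as well as at week 12, since the notes to Figure 2 describe a local reading at enrolment with a spare sample sent to the central laboratory.

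Make the between-arm change in NT-proBNP, preferably on the log scale, the first secondary endpoint, tested at two-sided 0.05 only if the primary is significant. The fixed order keeps the error over these two tests at 5%.

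If the sponsor prefers to keep both as primary, the protocol must state the rule and its consequences. An equal alpha split needs 177 evaluable per group for the responder test, or leaves it 71.1% power at 146. A both-must-succeed rule needs a power calculation that includes the change in NT-proBNP.

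The cost of the recommended change is a dated wording amendment before unblinding, and a matching registry update if the entry, which was not available here, also leaves the choice open. It needs no extra patients, visits or assays.
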